#### Qualitative process evaluation

Qualitative data will be analyzed using content analysis, guided by Graneheim and Lundman [21]. First, the transcribed material is read a number of times to get a general sense of the material by a group of researchers. Using the open code software for qualitative research, meaning units, which are key phrases in the text, are identified, condensed and outlined. Codes will then be ascribed to each meaning unit. The codes will be compared and grouped into sub-categories. This comparison will be performed consistently to identify emerging categories that will be further compared, re-organized and merged into sub-themes and one overarching theme. The coding and analysis process will be deductive in nature and involve key members of the research team.

### Economic evaluation

We will perform an economic evaluation to assess WelTel SMS from a healthcare payer perspective. The primary outcome of the cost effective analysis (CEA) will be the incremental cost per additional mother-infant pairs that remain in PMTCT until infant is aged 24 months. A secondary outcome is averted infant HIV-infections at cessation of breastfeeding. For the cost-utility analysis the outcome will be quality adjusted life years (QALYs), based on responses to the SF-12 and EQ5D. For both analyses (CEA and CUA) we will report the incremental cost-effectiveness ratios (ICERs) that will be computed as the ratio of the incremental costs to provide WelTel SMS over usual care and incremental effects e.g. cost per additional mother-infant pairs that remain in PMTCT until infant is aged 24 months, cost averted infant HIV-infections at cessation of breastfeeding and cost per QALY.

A secondary analysis will also consider the incremental cost per averted deaths by bringing infants lost to follow up back and enabling treatment. Thus, we will determine ICER for cost per averted deaths. Deterministic sensitivity analysis will be to address uncertainty.

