**Methods:**

WelTel PMTCT is a four to seven-centers, two-arm open randomized controlled trial (RCT) that will be conducted in urban and rural Kenya. Over 36 months, we plan to recruit 600 pregnant women at their first antenatal care visit and follow the mother-infant pair until they are discharged from the PMTCT program (when infant is aged 24 months). Participants will be randomly allocated to the intervention or control arm (standard care) at a 1:1 ratio. Intervention arm participants will receive an interactive weekly SMS ‘How are you?’ to which they are supposed to respond within 24 h. Depending on the response (ok, problem or no answer), a PMTCT nurse will follow-up and triage any problems that are identified.

The primary outcome will be retention in care defined as the proportion of mother-infant pairs coming for infant HIV testing at 24 months from delivery. Secondary outcomes include a) adherence to WelTel; (b) adherence to antiretroviral medicine; (c) acceptance of WelTel and (d) cost-effectiveness of the WelTel intervention.

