### Research hypothesis

The weekly interactive mobile phone SMS (WelTel) is an effective as well as cost-effective method to improve the retention of women living with HIV and their newborns’ in PMTCT care (women living with HIV and their HIV exposed infants who successfully complete the program when infant is aged 24 months).

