#### Secondary outcomes

Adherence to the WelTel SMS intervention measured as the proportion of women living with HIV who do not respond to the SMS within 7 days.Adherence to (i) ARVs measured as the proportion of women living with HIV who do not respond to the SMS within 7 days when suspected to be out of ARVs (i.e. failure to pick up ARVs that can cover her absence); (ii) facility-based delivery measured as the proportion of women who deliver in hospital; (iii) early infant HIV testing defined as the proportion of HIV-exposed infants who are tested for HIV within 8 weeks of birth measured as HIV –exposed infants with known HIV status at age 10weeks and (iii) exclusive breastfeeding defines as feeding the HIV-exposed infant only milk from the mother’s breast.Participant perceived facilitators and barriers of the WelTel SMS intervention (assessed as perceived reasons and challenges of use as well as suggestions to possible solutions).Cost compared with (i) effectiveness (levels of retention) from a payers’ perspective and (ii) quality of life (differences in pregnant women’s QALYs between the two trial arms.

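### Deterministic sensitivity analysis is the only method named for uncertainty in the cost-effectiveness ratios, and by itself it does not quantify sampling error in retention and QALYs

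*Protocol article*

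**What the plan says.** The Research hypothesis section of the protocol article claims that the weekly SMS "is an effective as well as cost-effective method to improve the retention". Cost-effectiveness is therefore part of what the trial sets out to show, and the abstract says the economic results are meant to inform policy and possible scale-up.

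The Economic evaluation section names four ratios:

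- The primary one "will be the incremental cost per additional mother-infant pairs that remain in PMTCT until infant is aged 24 months".
- One concerns infections: "A secondary outcome is averted infant HIV-infections at cessation of breastfeeding".
- The cost-utility ratio uses "quality adjusted life years (QALYs), based on responses to the SF-12 and EQ5D".
- A further secondary analysis takes the "incremental cost per averted deaths by bringing infants lost to follow up back and enabling treatment".

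On uncertainty in these ratios the section has a single sentence: "Deterministic sensitivity analysis will be to address uncertainty". The Statistical methods section plans a 95% confidence interval for the relative risk of retention, but nothing carries that interval into the ICERs.

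**The concern.** A deterministic analysis sets chosen inputs to chosen values and recalculates the result. That suits quantities that are assumed, such as unit prices. The denominator of the primary ICER is different: it is a difference between two proportions estimated in this trial. QALYs likewise come from individual questionnaire responses. Both would change if another 600 women were sampled.

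Moving inputs one set at a time attaches no probability to the results and gives no joint distribution of incremental cost and incremental effect. A reader could not tell from it how likely it is that the intervention is worth its cost at a given willingness to pay. Since cost-effectiveness is in the hypothesis and is meant to guide scale-up, a point ICER with deterministic ranges could look much firmer than the data allow.

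**Working it through.** **Inputs.** All are from the Sample size section: control retention about 30%; difference 11 points, hence 41% with the intervention; 300 women per arm; 5% dropout; two-sided 5% level; 80% power. The Economic evaluation section gives no figure to reproduce, and no cost is stated anywhere. Let C be the incremental cost per woman, held fixed (an assumption).

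**Reproducing the planning figures.** The usual pooled two-proportion formula for 30% versus 41% gives 296 per arm, against the stated 300. Power is 80.5% with 300 per arm. After 5% dropout, 300 × 0.95 = 285 per arm, with power 78.5% and a smallest detectable difference of 11.2 points. The planning rates are therefore a fair basis for what follows, and the sample size is not in dispute.

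**Sampling error of the retention difference, 285 per arm.**

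SE = √[(0.30 × 0.70 + 0.41 × 0.59) / 285] = √(0.4519 / 285) = 0.0398

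95% CI = 0.11 ± 1.96 × 0.0398 = 0.032 to 0.188, or 3.2 to 18.8 points

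**Carrying it to the ICER per additional retained pair.** The ICER is C divided by the difference d. The multiples below use unrounded limits (0.03195 and 0.18805).

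- Point value: C / 0.11 = 9.1 C
- At the upper limit of d: C / 0.18805 = 5.3 C, which is 0.11 / 0.18805 = 0.58 times the point value
- At the lower limit of d: C / 0.03195 = 31.3 C, which is 0.11 / 0.03195 = 3.4 times the point value

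The two ends differ by a factor of 5.9. With all 300 per arm, the interval for d is 3.4 to 18.6 points and the ICER runs from 5.4 C to 29.5 C, a factor of 5.5.

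**Smaller observed effects, 285 per arm.**

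| Observed difference | 95% CI (points) | ICER range |
|---|---|---|
| 11 points | 3.2 to 18.8 | 5.3 C to 31.3 C |
| 8 points | 0.2 to 15.8 | 6.3 C to about 400 C |
| 5 points | −2.7 to 12.7 | unbounded, as d may be zero or negative |

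**Why net benefit is the safer scale.** Write λ for the amount a payer would give for one more retained pair. Net monetary benefit per woman is λ × d − C. At the planned effect, the point estimate favours the intervention once λ exceeds 9.1 C, but the lower 95% limit does so only once λ exceeds 31.3 C. For any λ between these values the point ICER would read as cost-effective while the 95% interval of net benefit includes zero. Net benefit also stays well defined when d is near zero, where the ratio does not.

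**The case against.** **Is this a detail left to a fuller plan?** A separate health-economic plan may add probabilistic methods. The article does not say that deterministic analysis is the only method, merely that it is the method named. That limits the wording, but the point stands: the article commits to a method for this purpose, and the method does not suffice alone.

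**Could a deterministic analysis show the range above?** Yes. Moving the effect across its confidence limits at fixed cost is itself deterministic, and a confidence interval for retention will be reported. A reader might infer that the ICERs must ignore sampling error, or that only one input at a time will be varied. The article says neither; it does not state which inputs will be varied or how. What remains is that such an analysis gives no joint cost-effect uncertainty and no probability of being cost-effective.

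**Are costs sampled from individuals?** This is not established. The Economic evaluation section speaks of the incremental cost of providing the service, from the payer's side. The Baseline section records participants' costs of reaching care, which are not clearly payer costs. The argument therefore rests on retention and QALYs, and the remedy must work where costs are not participant-level.

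**Infections averted.** The abstract speaks of "retention in care defined as the proportion of mother-infant pairs coming for infant HIV testing at 24 months from delivery", so a reader might infer that infections would be counted only in infants brought for testing, which would distort the comparison because the intervention aims to change attendance. The article gives no counting rule, so this cannot be held against it. Early infant testing is "measured as HIV –exposed infants with known HIV status at age 10weeks", so infants lost later may have a known status, and the ratio for deaths averted suggests that estimation beyond observed counts may be intended. Putting a size on such a bias would also mean using 24-month retention as a testing rate, and choosing between the national 14% transmission and the figure below 2% with antiretrovirals, both in the Background. How infections are estimated is a detail that a condensed article may leave open.

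**Conclusion.** The point holds for the uncertainty method. Deterministic sensitivity analysis is the only one named for four ICERs, and alone it does not quantify sampling error in retention and QALYs or the joint uncertainty of cost and effect. At the planned effect with 285 per arm, sampling error in retention alone moves the primary ICER from about 0.58 to 3.4 times its point value; if the interval for the difference reaches zero, the ICER has no finite bound. These figures assume the planning rates, a normal-approximation interval and a fixed incremental cost. Uncertainty in cost, and its correlation with effect, are not included because the article gives nothing from which to calculate them.

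The matter concerns secondary economic outcomes and leaves the primary retention analysis untouched. It is still worth correcting, because cost-effectiveness is in the hypothesis and the change is cheap.

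**What to change.** Name a stochastic analysis as the main uncertainty analysis for the ICERs:

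- Use a non-parametric bootstrap of participant-level retention and QALYs, resampled within arm and clinic, since randomisation is done separately at each clinic.
- Resample costs together with effects where they are recorded per participant. Where they are known only at programme level, draw them from stated probability distributions.
- Report 95% limits for incremental cost and for incremental effect, net monetary benefit with its interval, and a cost-effectiveness acceptability curve over a range of willingness-to-pay values.
- Keep deterministic analysis for unit costs and other assumed inputs.

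This takes a few sentences in the plan and a little more analysis work. Because costs that are not participant-level receive distributions, the change does not depend on collecting individual payer costs. The other price is an ICER that looks less precise.

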## Discussion

This trial provides an opportunity to test whether the WelTel SMS intervention is effective in improving retention in PMTCT care. Further, we will be able to determine whether the interactive WelTel text-messaging intervention, by engaging patients with the PMTCT clinic on a weekly basis, is a cost-effective way to improve retention in this critical stage of care, potentially helping to eliminate pediatric HIV infections.

## Abbreviations

AIDS, acquired immune deficiency syndrome; ANC, antenatal care; ART, antiretroviral therapy; ARVs, antiretroviral drugs; CEA, cost effectiveness analysis; CUA, cost utility analysis; HIV, human immunodeficiency virus; ICERs, incremental cost effectiveness ratios; IDIs, in-depth interviews; IREC, Institutional review and ethics committee; MCH, maternal and child health; MTCT, mother to child transmission; PIP, partners in prevention – Moi University; PLHIV, people living with HIV; PMTCT, prevention of mother to child transmission; QALYs, quality-adjusted life years; RCT, randomised clinical trial; RR, relative risk; SMS, short message service; UNAIDS, Joint United Nations programme on AIDS; WelTel SMS, Weekly mobile phone short message service
